### Strategies to improve adherence to intervention

Study retention will be promoted by a phone call 6 weeks after intervention has ended. The content of the training program will change weekly as the patient improves to promote motivation.

### Magnetic resonance imaging

At baseline, after the 4-week intervention and 12 weeks later whole-brain MRI scans will be acquired with a 3 T Philips Achieva scanner (Philips, Amsterdam, The Netherlands). The structural MRI protocol includes T1-weighted, T2-weighted, and fluid-attenuated inversion recovery (FLAIR) sequences and diffusion-weighted imaging (DWI). Functional brain mapping will include task-related blood oxygen level-dependent, functional MRI (BOLD-fMRI), and brain perfusion measurements with pulsed continuous arterial spin labeling (pcASL). Table 2 gives a detailed description of each sequence.

**Table 2 Tab2:** MRI acquisition details

Sequence	T1W	T2W	FLAIR	fMRI BOLD	pcASL	DWI
Voxel size (mm)	0.85 × 0.85 × 0.85	0.85 × 0.85 × 0.85	1.0 × 1.0 × 1.0 mm	3.00 × 3.05 × 3.00	3.00 × 3.08 × 6.00	2.00 × 2.04 × 2.00
FoV (mm)	245 × 245 × 208	1245 × 245 × 190	256 × 256 × 202	192 × 192 × 126	240 × 240 × 126	224 × 224 × 100
TR (ms)	7000	2500	4800	2490	4607	7700
TE (ms)	3.3	265	314	30	18	64
Flip angle	8°	35°	40°	80°	90°	90°/180°
Acquisition time (min:sec)	05:40	06:32	05:40	05:06^a^	09:26	05:31 + 0:53
Readout method (EPI, FEE, TFE, TSE)	TFE 243	TSE 133	TSE 182	FFE/EPI	FFE/EPI	PGSE/EPI
SENSE/TSE/halfscan factor	SENSE 2 (AP)	SENSE 2 (AP), 1.8 (RL)	SENSE 1.8 (AP), 1.9 (RL)	n.a	SENSE 2.0 (AP)	Halfscan factor 0.8 SENSE 2 (AP)
Other			Inversion time: 1650 ms	Monitoring of respiration and pulse (PhysioLog)	Post-label delay: 2 s	b = 1000 s/mm^2^ (gradient ampl. = 62mT/m, duration = 12.5 ms, separation = 27.5 ms) 40 gradient directions and 6 interleaved b = 0 Additional 5 b = 0 scans in the AP-PA direction every five condition

^a^Sequence repeated three times

#### Task-related fMRI

Task-related fMRI will employ two runs featuring different manual motor tasks: The first fMRI paradigm records BOLD signal changes during a unimanual index-finger tapping task. Participants will produce irregular finger taps in response to a central visual cue at a pace of 0.5 Hz with a jitter of 0.25 s. The task will be performed in a single fMRI run, lasting 5 min. The second fMRI paradigm uses a block design to probe BOLD signal changes during a visually cued bimanual motor task. In the bimanual paradigm, participants have to generate bimanual responses with their index fingers in four visually cued conditions, “left before right finger,” “right before left finger,” “simultaneous index finger response,” or “no press” in a pseudorandomized order. Each task condition is presented in a pseudorandomized order in blocks of 20 s for a total of 5 min. In each condition, button presses will be triggered by a central visual cue at a pace of 0.5 Hz with a jitter of 0.25 s. The bimanual fMRI paradigm will be tested in two fMRI runs, lasting 5 min each. See Supplemental Figure S4 for an illustration of the visual cues.

All patients will be trained prior to each scan session to ensure an accurate and consistent performance of the motor tasks. Motor performance will be recorded with a four-button bimanual hand-held response pad (Cambridge Research System, Cambridge, UK). The visuomotor tasks are programmed with PsychoPy® [41] and visual cues were presented on an MRI-compatible screen behind the scanner on a mirror mounted on the head coil.

#### Arterial spin labeling (ASL)

Whole brain perfusion maps will be measured by pulsed-continuous ASL (pcASL). See Table 2 for sequence details. Post-label delay is set for 2 s as recommended in an elderly population [42]. Patients are instructed to relax and stay awake during the ASL. We will use pcASL to compare changes in whole brain perfusion from baseline to follow-up between the patients receiving active vs. sham TDCS, respectively.

#### Diffusion-weighted imaging (DWI)

DWI of the brain will be done to segment the CST and transcallosal motor fiber tract that connects the left and right M1-HAND and to characterize the microstructural damage of these motor white-matter tracts. The details of the MRI sequence used for DWI are described in Table 2. Using a diffusion tensor model, we will evaluate fractional anisotropy (FA) and mean diffusivity (MD) in the CST between the affected and unaffected hemispheres. Regional MD is acutely reduced after stroke but decreases to or below normal values in the weeks after infarct, reflecting a loss in cell density and tissue integrity [43–45]. Regional FA is a voxel-wise measure of the directionality of water diffusion and is sensitive to axonal alignment, density, and integrity [46]. A disruption of corticospinal tract integrity by a stroke lesion increases regional FA in the ipsilesional CST resulting in a FA asymmetry between the affected and the unaffected hemisphere [45, 46]. Tract segmentation will be performed with TractSeg [47] combined with custom MATLAB (MathWorks) scripts as a quantitative biomarker of microstructural white matter changes.

### Transcranial magnetic stimulation

Single- and paired-pulse TMS is performed at pre-interventional baseline and at either one or both follow-up visits to estimate the integrity of the CST as well as to evaluate corticomotor excitability. Specifically, the maximal amplitude of the motor evoked potential (MEP), cortico-motor conduction time (CMCT), contralateral silent period (cSP), ipsilateral silent period (iSP), and short intracortical inhibition (SICI) [48, 49] will be measured. TMS will be delivered with a hand-held figure-of-eight coil (MC-B70) connected to a MagPro 100 option stimulator (MagVenture, Farum, Denmark). The TMS evoked motor responses will be recorded with self-adhesive surface electrodes (Neuroline 700, Ambu, Ballerup, Denmark) attached to the left and right contralateral first dorsal interosseus (FDI) muscle using a belly-to-tendon montage. Electromyographic signals will be sampled at 5 kHz, band-pass filtered (5–2000 Hz) and amplified (1000), digitized, and stored using an eight-channel DC amplifier (1201 micro Mk-II unit, Digitimer, Cambridge Electronic Design) and Signal software version 4.11 (Cambridge Electronic Design, Cambridge, UK).

The cortical motor hotspot, the scalp position at which TMS produces the largest MEP, will be determined functionally and recorded using stereotactic neuronavigation (Localite, Bonn, Germany) throughout the experiment to ensure precise coil positioning. Resting motor threshold (RMT) will be determined as the stimulation intensity eliciting an MEP of > 50 mV in 5 out of 10 stimulations [50] and active motor threshold as an MEP of > 200 mV and a visible cortical silent period during a 10% maximal voluntary contraction (MVC) (if possible).

We will evaluate the excitability of intracortical GABAergic inhibitory circuits by measuring the strength of short intracortical inhibition (SICI) with paired-pulse TMS, applying a conditioning stimulus at an intensity of 80% RMT 2.1 ms prior to a test stimulus at an intensity of 120% RMT [51]. Twenty conditioned MEPs and 20 non-conditioned MEPs will be recorded to obtain reliable estimates of MEP amplitude for each stimulation condition.

Transcallosal inhibition will be estimated by recording the iSP. To this end, 20 pulses at 150% of RMT will be applied, while the patient performs a 50% MVC of the FDI muscle ipsilateral to the stimulated hemisphere. Lastly, maximum MEP amplitude, corticomotor MEP latency, and cSP will be determined using 20 TMS pulses at 150% RMT during 10% MVC of the contralateral hand. Moreover, we will determine the M-wave and F-wave latencies from 20 supramaximal constant current ulnar nerve stimulations (Digitimer DS7A, Cambridge, UK) to determine CMCT [48].

### Field modeling and electrode positioning

The scalp location of the TDCS center electrode and current intensity will be individualized using a SimNIBS pipeline based on the T1- and T2-weighted images of the individual patient [25, 40].

A custom SimNIBS script (SimNIBS version 4.0) will determine both the current intensity necessary to reach a mean field strength of 0.2 mV/m as well as locate the position of the target electrode on the scalp of the patient using a mask drawn in *fsaverage* for the hand knob area on either left or right hemisphere depending on location of the stroke lesion [52].

The position of the target electrode will be visualized on a 3D head mesh using a custom SimNIBS script displaying the three nearest EEG positions corresponding to a 64-channel EasyCap® M10-layout EEG-cap (EasyCap_BC_TMS64_X21, EasyCap, Woerthsee-Etterschlag, Germany). See Fig. 3. An individual EasyCap EEG-cap will be fitted for each patient prior to starting the intervention on which the position of the target electrode is marked with a hole. This is used to mark and ensure consistent electrode positioning during the intervention period. Surround electrodes will be positioned in 60 mm equally distributed as a ring around the target electrode. Five landmark positions will be used to ensure consistent fitting of the cap between sessions (Cz, Fpz, and Iz for frontal alignment and T8 and T7 for left–right-alignment).

**Fig. 3 Fig3:**
[figure not shown]
The use of SimNIBS to determine the current strength of TDCS necessary to reach a field strength of 0.2 mV/m in the target area as well as the distance from the target point to EEG positions on a head mesh to transfer the target position to a position of the scalp in real life

### Primary outcome

The primary outcome is the difference in change of FMA-UE score at follow-up after 4 weeks of intervention compared to baseline between active TDCS vs. sham-stimulation.

The FMA probes five domains: motor function, sensation, balance, joint pain, and joint range of motion in the upper and lower extremities of hemiplegic stroke patients. It can be performed as either full-FMA or as upper or lower extremity FMA (FMA-UE or FMA-LE, respectively). In this study, FMA-UE will be assessed. Each of the five domains contains different items for assessment which are scored on a 3-point scale: 0 = cannot perform. 1 = performs partially, and 2 = performs fully. Impairment severity is based on FMA motor scores. Maximum score for FMA-UE is 66 points [53, 54].

### Secondary outcomes

#### Motor function and activity

Difference in improvement in upper-extremity function from baseline to follow-up in the active and sham-group will also be assessed with Action Reach Arm Test (ARAT). ARAT is composed of 19 items categorized into four subscales (grasp, grip, pinch, gross movements) arranged hierarchically with decreasing difficulty Task performance is rated on a 4-score scale ranging from 0 = “no movements” to 3 = “movements performed normally” [55]. Additionally, we will register the time spend on each task because the time frame resulting in the score of 2 (“task completed”) is large covering from 5 to 60 s. The Action Research Arm Test (ARAT) is currently being validated to the Danish language in a separate study by co-author [name] (ID: H-20046644).

Changes in stroke severity and daily activity will be assessed by the National Health Institutes Stroke Scale (NIHSS) score, Modified Rankin Scale (mRS) [56], 20-item Barthels Index (BI-20) [57], 10-m-walk-test [58]. See also Table 3 as well as S3.

**Table 3 Tab3:**
[figure not shown]
SPRIT-figure: schedule of study procedures

*SDMT* symbol digit modalities test, *MoCA* Montreal Cognitive Assessment, *IQCODE* Informant Questionnaire on Cognitive Decline in the Elderly, *BDI-II* Beck’s Depression Inventory II, *FSS* Fatigue Severity Scale, *WHO-5* World Health Organization – Five Well-being Index, *PAS2* Physical Activity Scale 2, *UE-FMA* Upper-extremity Fugl-Meyer Assessment, *ARAT* Action Reach Arm Test, *BI-20* Bartel-20 Index, *10MWT* 10-m walk-test, *MEP* motor evoked potential, *SICI* Short interval intracortical inhibition, *iSP* ipsilateral silent period, *CMCT* cortico-motor conduction time

#### Cognition

Baseline cognitive level will be evaluated by Informant Questionnaire on Cognitive Decline in the Elderly (IQCODE*)* [59, 60]. Cognitive changes will be assessed by Montreal Cognitive Assessment (MoCA) [61] and Symbol Digit Modalities Test (SDMT) [62]. See also Table 3 as well as S3.

#### Fatigue, mental well-being, and degree of depression

*Fatigue* will be examined by the Fatigue Severity Scale (FSS) [63]. *Mental well-being* will be evaluated by the EQ-5D-5L-test of health [64] and the World Health Organization – Five Well-Being Index (WHO-5) [65]. The degree of depression will be evaluated by Beck’s Depression Inventory-II (BDI-II) [66]. See also Table 3 as well as S3.

All tests and questionnaires used have been validated for stroke patients and are available in the Danish language.

#### Motor network connectivity and interhemispheric imbalance

Changes in the interactions between the motor network structures of the affected and unaffected hemispheres are important as they correlate with motor recovery. They will be assessed by effective connectivity during task-related fMRI. Using dynamic causal modeling (DCM) the direct influence (either facilitatory or inhibitory) of one region of interest (ROI) over another can be estimated (Friston [67]). The ROIs of this study are the primary motor cortex (M1), the supplementary motor area (SMA), and the ventral and dorsal premotor cortex (vPMC and dPMC, respectively) as these areas are involved in the motor network disturbances after stroke [68, 69]. Furthermore, the imbalance in the degree of activation of the motor cortex in the affected vs unaffected hemisphere will be determined by the laterality index (LI), as this is also correlated with motor recovery and tends to change to a more balanced activation with recovery [70].

#### Blood samples

A battery of routine blood samples (basic lab) will be collected at baseline and at each follow-up visit for safety and evaluation of cardiovascular risk factors (hemoglobin, hematocrit, leukocytes, C-reactive protein, blood platelets, international normalized ratio (INR), activated partial thromboplastin time (aPTT), fibrinogen, high-sensitive CRP (hsCRP) and apolipoprotein(a) (LP(a)). Additional blood will be collected at baseline for genetic analysis of brain-derived neurotrophic factor (BDNF) Val66Met genetic polymorphism, since this allele variant may influence the effect of TDCS [71] (De la Rosa 2019). Furthermore, blood for determination of plasma levels of cathepsin B will be collected at baseline and at each follow-up visit for measurements, as this lysosomal protein may relate to the cognitive effects of exercise [72]. See also Table 3 as well as S3.

### Participant timeline

All patients will be assessed at baseline directly after enrolment and at follow-up1 (after the 4 weeks of intervention has ended) and follow-up2 (12 weeks post-interventions).

See Table 3 for SPIRIT-figures of study procedures, Fig. 4 for a study flowchart, and Fig. 5 for a graphical synopsis of the study protocol.

**Fig. 4 Fig4:**
[figure not shown]
The PRACTISE-trial flow diagram

**Fig. 5 Fig5:**
[figure not shown]
A graphical synopsis of the PRACTISE trial

### Sample size

The sample size is calculated based on the primary outcome. We expect an average difference in UE-FMA between groups of 5 points with a standard deviation of 3–4 points [23]. Assuming a Type I error of 0.05 and a Type II error of 80% 12 participants per arm are needed to reach sufficient power. To account for dropouts, we will include a minimum of 15 patients in each arm. An interim analysis will be done after the inclusion of 24 patients. To consider any differences due to the location of the stroke lesion we aim to include 30 patients with a cortical stroke lesion and 30 patients with a subcortical stroke lesion. However, if recruitment is more challenging than expected a feasibility analysis will be done after the inclusion of 30 stroke patients stratifying for infarct location (cortical vs. subcortical) in the analysis.

### Recruitment

Eligible patients will be identified by daily screening of medical records, and they will be provided with both oral and written information about the study. In case of severe aphasia, a next of kin participating in the information meeting may co-sign the consent if the patient wishes to participate in the study.

## Methods: assignment of intervention

### Allocation and sequence generation

Patients will be randomized consecutively into two groups, active or sham-stimulation, based on equal allocation. The allocation sequence is generated by SealedEnvelope™ (London, UK). Random-sized permuted blocks of participants will be applied at randomization. No stratification.

### Allocation concealment and implementation

At randomization, each patient is assigned a unique 5-digit code which will be typed into the DC-stimulator before each stimulation to apply either “active” or “sham” stimulation to maintain double blinding.

The randomization key containing the order of blocks and the allocation to either active or sham TDCS will be kept secured and unavailable to any delegates who are connected to the study until the trial is complete or in case an emergency unblinding is needed.

### Blinding

To remove any sensation of the TDCS the skin under the electrodes will be prepared with surface analgesics (Emla crème ®) 15 min prior to each stimulation. After each intervention session, the patient will be asked about any sensations from TDCS (such as skin itch, dizziness, headache).

At the last follow-up visit the patients will be asked: “Do you think you got active TDCS? Yes or no” for a quality assessment of the blinding. Furthermore, they will be asked: “Would you recommend TDCS and training for other stroke patients? Yes or no” for an assessment of feasibility.

### Statistical methods

All variables will be tested for normal distribution prior to analysis and logarithmically transformed if necessary. If data diverge from the normal distribution after transformation non-parametric testing will be performed. All tests will be two-sided and P < 0.05 will be considered significant. Data will be analyzed using Microsoft Excel 2010 (Microsoft Corporation, Redmond, WA, USA), *R* (version 3.6.1)*,* and REDCap or similar software. Statistical planning is conducted in a corporation with a biostatistician.

All data will be analyzed for the intention-to-treat population. All patients with complete outcome data will be analyzed according to the group they were randomized to. All available data for each patient will be included in the analysis. Missing data will be analyzed using imputation. Estimated treatment effects will be calculated based on a constrained longitudinal data analysis (cLDA) which will provide a result unbiased by values missing at random.

At follow-up 1 and follow-up 2 immediately after and 12 weeks after the intervention, respectively, a linear mixed model analysis will be used for both primary and secondary outcomes using cLDA. No other independent variables will be included in the analysis. The effect size will be calculated as mean change from baseline to follow-up and given as mean estimates of differences with a 95% confidence interval (CI). Patients that do not show up for a follow-up visit will be counted as missing values for the specific assessment point meant to be evaluated at that particular follow-up visit.

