### Eligibility criteria

Inclusion criteria for the patients are ischemic stroke lesion either located cortically or subcortically in the large hemispheres, symptoms presenting with any degree of arm paresis, age ≥ 18 years, able to speak and read Danish, and able to give informed consent and index stroke within 28 days of inclusion.

Exclusion criteria are > 50% stenosis of extra- or intracranial vessels, > 1 cerebral infarct or stroke event during admission, cerebral aneurysms or cerebral arterio-venous malformations, stroke location outside the large hemispheres, cognitive dysfunction interfering with the ability to participate, history of seizures, epilepsy or epilepsy in first-degree family, anxiety, dementia, alcohol- and drug abuse, headaches > 16 days per month or migraine as these can be provoked by TDCS and TMS, current use of neuro-receptor/transmitter modulating medication, medication reducing seizure threshold or prior adverse effect to TDCS or TMS, contraindications to MRI, or claustrophobia.

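### The Statistical methods section gives two unreconciled rules for the primary FMA-UE analysis: a normality-driven switch for all variables and an unconditional cLDA mean difference

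*Protocol article*

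**What the plan says.** The Statistical methods section opens with a general rule: "All variables will be tested for normal distribution prior to analysis and logarithmically transformed if necessary". The next step is "If data diverge from the normal distribution after transformation non-parametric testing will be performed". No variable is exempted, and the non-parametric test is not named.

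Two paragraphs later the section assigns primary and secondary outcomes at both follow-ups to a linear mixed model fitted as a cLDA. No condition is attached. Effects are mean changes from baseline, "given as mean estimates of differences with a 95% confidence interval (CI". The section justifies cLDA by its lack of bias when values are missing at random.

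Elsewhere in the article:

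- Primary outcome: the between-arm difference in FMA-UE change from baseline to the end of the 4-week intervention. "Maximum score for FMA-UE is 66 points".
- Eligibility criteria: "symptoms presenting with any degree of arm paresis", with no upper or lower FMA-UE limit.
- Sample size: based on a 5-point difference between groups with an SD of 3–4 points.

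**The concern.** FMA-UE falls under both rules, and they can give different analyses. An analyst who followed either could claim to have followed the protocol.

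The general rule also suits this endpoint badly:

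- The primary outcome is a change, which can be zero or negative, where a log is undefined. A raw score of 0 raises the same problem.
- The scale is capped at 66 and mildly affected patients may enter, so left skew is possible. A log makes left skew worse.
- A mixed model assumes roughly normal residuals, not normally distributed raw variables.

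If the rule were applied to FMA-UE, the effect could be expressed in points, as a ratio or in ranks, depending on the data. A two-group rank test on change would not estimate the 5-point mean difference used for the sample size. It would also leave out patients without the follow-up value, whom cLDA keeps through their baseline value. Since a normality test rejects more often as numbers grow, the planned interim analysis and the final analysis could end on different branches.

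**Working it through.** **1. The plan's own figure.** Inputs from Sample size and Statistical methods: difference 5, SD 3–4, "Assuming a Type I error of 0.05", two-sided ("All tests will be two-sided and P < 0.05 will be considered significant"), and "a Type II error of 80% 12 participants per arm are needed to reach sufficient power". I read the last as 80% power, because that reproduces the stated n.

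n per arm = 2(1.960 + 0.842)² × SD² / 5²

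- SD 4: 2 × 7.85 × 16 / 25 = 10.05, so 11. The t-test version gives 11.1, so 12. **The stated 12 reproduces.**
- SD 3: 2 × 7.85 × 9 / 25 = 5.65, so 6. The t-test version gives 6.8, so 7.

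**2. Cost of ranks alone (SD 4).** Divide the t-test n by the relative efficiency of the rank test:

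- normal data: 11.1 / 0.955 = 11.6, so 12
- worst case for a location shift: 11.1 / 0.864 = 12.8, so 13

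Both are below the planned minimum of 15 per arm. Ranks by themselves do not break the design.

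**3. Is the log step usable on a change score?** Assume a sham gain of 6 or 8 points with SD 4, ignoring the cap.

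- P(change ≤ 0) = Φ(−6/4) = 0.067, or Φ(−8/4) = 0.023.
- Chance of at least one such patient among 15 sham patients: 1 − 0.933¹⁵ = 0.65, or 1 − 0.977¹⁵ = 0.29.

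So the log could often not be computed without an offset, and the article specifies none.

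**4. How often the rule would reach a rank test, and what that costs.** Assumptions that are not in the documents:

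- Baseline is 66 × Beta(3,1) (mean 49.5) or 66 × Beta(2,1) (mean 44), both left-skewed.
- Gain is 6 points on sham and 11 on active, SD 4, with scores rounded and capped at 0–66. About 25–35% of follow-up scores then sit at 66.
- The fixed analysis is baseline-adjusted ANCOVA, the two-visit stand-in for cLDA with complete data.
- The rule uses Shapiro–Wilk, and its fallback is Mann–Whitney on change. On the score, log(score + 1) is tried first; on the change, every failure goes straight to the rank test.

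The article does not say which variable is tested, so both readings are shown. Each cell gives power as fixed vs rule, for Beta(3,1); Beta(2,1).

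| Per arm | Follow-up score tested | Change score tested | Rank test reached when change is tested |
|---|---|---|---|
| 12 | 0.55 vs 0.42; 0.59 vs 0.50 | 0.53 vs 0.52; 0.60 vs 0.59 | 9–12% |
| 15 | 0.65 vs 0.51; 0.72 vs 0.62 | 0.65 vs 0.61; 0.72 vs 0.70 | 11–17% |
| 30 | 0.94 vs 0.83; 0.96 vs 0.91 | 0.92 vs 0.89; 0.96 vs 0.95 | 19–30% |

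When the follow-up score is tested, the rank test is reached in 87–100% of trials. The two power columns come from separate runs of 3,000 and 1,500 trials per cell, so the fixed values differ by up to 2 points. Simulation error is about 1 point (√(0.25/1,500) = 0.013). With a symmetric baseline, 66 × Beta(2,2), the loss was nil. The log moved skewness from −0.6/−0.9 to −1.8/−1.9.

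**5. Sensitivity to the size of the ceiling.** This second set uses truncated normal baselines, gain 8, SD of change 4, true difference 5, and tests the follow-up score (2,000 trials per cell).

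| Assumed baseline mean/SD | Scores at 66 | Rank test reached | Power lost, 12 to 30 per arm |
|---|---|---|---|
| 30/8 | 0% | 2–3% | about 0 points |
| 45/12 | 22% | 69–100% | 3–7 points |
| 52/10 | 39% | 98–100% | 16–19 points |
| 56/8 | 54% | 100% | 18–36 points |

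Mann–Whitney and the t-test on change differed by at most about 4 points, so the loss comes mainly from dropping the baseline-adjusted model. Type I error of the rule was 0.04–0.05.

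**The case against.** The best defence is that the specific sentence governs. The opening rule is generic and may be meant for the many laboratory, MEP and imaging measures, whereas the cLDA sentence names the primary outcome and carries no condition. That reading is natural, and it means the article does not state that the primary analysis switches. It does not settle the matter, because the opening rule says it covers every variable and no order of precedence is given.

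A reader might go further and infer that cLDA would probably be abandoned for FMA-UE and that the trial would lose power. The documents do not support this. They give no baseline FMA-UE distribution and mention no ceiling; entry with any degree of paresis admits severe as well as mild cases. No rank test is named, and nothing says baseline adjustment would be dropped. If the change score, which is the stated primary outcome, is what gets tested, the rank test is reached in a minority of trials even under the left-skewed assumptions. Much of the low absolute power in those scenarios comes from the assumed ceiling itself, which fixing the analysis would not remove.

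It also stands that false-positive risk is not raised, and that the article describes its framework as exploratory. A plea that the detail belongs in the SAP does not help: the rule is written in the article, and the objection is to what it says.

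**Conclusion.** The contradiction is real and rests on the text alone: one section gives two rules for the primary outcome and does not rank them. The log step is unsuitable for a change score and for a scale bounded above. A simple rank test would not deliver the promised mean difference or the missing-at-random property for which cLDA was chosen.

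The effect on power is conditional on an assumed ceiling, on the variable tested and on a fallback without baseline adjustment:

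- about nil without a ceiling
- about 1–5 points if change is tested, and about 5–15 if the raw follow-up score is tested, with 25–35% of follow-up scores at 66
- larger only under heavier assumed ceilings with the raw score tested

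Type I error stays near 5%. This should be fixed, but it does not threaten the validity of the trial.

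**What to change.** In Statistical methods:

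1. State that the primary analysis is cLDA on untransformed FMA-UE points, whatever a normality test shows.
2. Exempt FMA-UE and the other clinical scales analysed by cLDA from the test-and-transform rule.
3. Replace normality testing of raw variables with a check of model residuals for these outcomes.
4. Keep any transformed, rank or permutation analysis of FMA-UE as an optional sensitivity analysis that cannot replace the primary result.

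The cost is a few sentences and, if chosen, one sensitivity analysis. Sample size, visits and data collection do not change.

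### Limiting the analysis to patients with complete outcome data contradicts the intention-to-treat, all-available-data and cLDA statements around it, and imputation is given no stated role

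*Protocol article*

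**What the plan says.** Everything at issue is in the Statistical methods section of the protocol article, mostly in consecutive sentences.

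- Population: "All data will be analyzed for the intention-to-treat population". The set is not defined further.
- Next sentence: "All patients with complete outcome data will be analyzed according to the group they were randomized to".
- Data used: "All available data for each patient will be included in the analysis".
- Missing values: "Missing data will be analyzed using imputation". No role or order relative to the main model is given.
- Estimator: "Estimated treatment effects will be calculated based on a constrained longitudinal data analysis (cLDA) which will provide a result unbiased by values missing at random".
- Model, for follow-up 1 and follow-up 2: "a linear mixed model analysis will be used for both primary and secondary outcomes using cLDA".
- Missed visits: "Patients that do not show up for a follow-up visit will be counted as missing values for the specific assessment point".

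No sentence says which population rule prevails where they differ.

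**The concern.** With complete cases only, there is nothing to impute and no missing value for cLDA to handle. The complete-data sentence therefore cannot operate alongside those that follow it. Two analysts could follow the section faithfully and analyse different sets of patients.

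Missing outcomes are foreseeable. The Sample size section raises the target from 12 to at least 15 per arm for dropouts. The Criteria for discontinuation section takes patients out of the study for too few completed sessions, for stimulation side effects and for inability to complete the MRI scans. At least the side-effect route could plausibly operate differently under active and sham stimulation, and unequal loss is the situation in which a complete-case analysis can mislead. An interim analysis is also planned, so the rule should be settled before any results are seen.

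**Working it through.** **1. The plan's own sample size.** Inputs from the Sample size section: difference 5, SD 3–4, type I error 0.05, and 80%, which is printed as a type II error and read here as power. Tests are two-sided (Statistical methods).

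- Normal approximation: n per arm = 2 × (1.960 + 0.842)² × SD² / 5².
- At SD 4: 2 × 7.85 × 16/25 = 10.05, so 11. The t-test version gives 12, with power 83.3%. This reproduces the stated 12.
- At SD 3 the t-test version gives 7, so the stated 12 rests on the upper SD.
- Implied loss: 1 − 12/15 = 20%; check: 12/(1 − 0.20) = 15.

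**2. Who is analysed under each reading.**

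| FMA-UE observed at | Complete = all visits | Complete = baseline and follow-up 1 | All available data, cLDA |
|---|---|---|---|
| Baseline, follow-up 1, follow-up 2 | in | in | in |
| Baseline, follow-up 1 | out | in | in |
| Baseline, follow-up 2 | out | out | in |
| Baseline only | out | out | in, adds little to the contrast |

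Neither meaning of complete matches the last column, which is what the all-available-data sentence, the cLDA sentences and the missed-visit sentence describe.

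**3. How many patients.** Complete cases = N × (1 − loss).

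| Loss | N = 30 | N = 60 |
|---|---|---|
| 10% (assumed) | 27 | 54 |
| 20% (implied by 12 to 15) | 24 | 48 |
| 30% (assumed) | 21 | 42 |

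Under cLDA on available data, all 30 or 60 contribute at least a baseline value.

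**4. Whether it can move the estimate.** The difference of 5 and the SD of change of 4 come from the Sample size section, and 30 per arm from the anticipated 60 patients. The rest are assumptions: baseline mean 40 and SD 12; mean change 6 (sham) and 11 (active), falling by 0.15 per baseline point; follow-up 1 always observed; 3,000 simulated trials per setting. Follow-up 2 is missing with

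logit P(missing) = −1.5 + k × (follow-up 1 change − that arm's mean change),

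which removes 18% to 21% of patients. The complete-case estimate is the difference in mean follow-up 1 change among patients with both visits. A baseline-adjusted comparison of everyone stands in for cLDA.

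| k active | k sham | Complete cases | All data |
|---|---|---|---|
| 0 | 0 | 4.97 | 4.99 |
| −0.2 | −0.2 | 4.98 | 4.99 |
| −0.2 | 0 | 5.58 | 4.99 |
| 0.2 | −0.2 | 3.77 | 4.99 |
| −0.2 | 0.2 | 6.20 | 4.99 |

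Against the true 5, the complete-case error runs from 3.77 − 5 = −1.23 to 6.20 − 5 = +1.20 when the mechanism differs by arm. It is negligible when missingness is random or follows the same mechanism in both arms. Here the same mechanism means the same dependence on change relative to each arm's own mean. The simulation takes complete to mean all visits; under the baseline-and-follow-up-1 meaning, no patient in it would be dropped.

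**The case against.** The best defence is that most of the section points one way. cLDA is named twice, for the treatment effect and for primary and secondary outcomes, and the missed-visit sentence follows available-data logic. On that view the complete-data sentence is a loose way of saying that patients are analysed as randomised. This is a fair reading, and it defeats several stronger conclusions that a reader might draw:

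- *That the estimator is not fixed.* It largely is: cLDA in a linear mixed model. What is open is the data fed to it and the place of imputation.
- *That the intention-to-treat claim fails.* It fails only if the complete-data sentence governs.
- *That imputation and cLDA are incompatible.* They are not. Imputation can precede cLDA, can serve as a sensitivity analysis, and can draw on auxiliary measures that the model leaves out. The fault is that its role is unstated.
- *That the imputation would inflate the type I error.* That requires a crude single fill. The article names no imputation method, and its type can be left to the analysis plan, so no such figure can be attached to this protocol.
- *That complete cases are always biased.* The simulation shows otherwise.

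It is also true that the primary outcome uses only baseline and follow-up 1. If complete means those two visits, the practical gap to cLDA is small. Fifteen per arm is a minimum, 60 patients are anticipated, and the trial calls its framework exploratory.

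What survives is the contradiction itself. The sentence is current text, it restricts the population on its plain meaning, and nothing subordinates it to the others. This is conflicting text rather than detail deferred to an analysis plan.

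**Conclusion.** The point holds in this limited form. The complete-data sentence contradicts the intention-to-treat population, the use of all available data, the stated reason for choosing cLDA ("which will provide a result unbiased by values missing at random") and the missed-visit rule. Imputation is added without a role.

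The size depends on which sentence is followed. If the complete-data sentence governs, 6 of 30 or 12 of 60 randomised patients are left out at the implied 20% loss. The estimate can then be off by about 1.2 points on an expected 5 in the least favourable simulated settings, and by almost nothing when missingness is random or follows the same mechanism in both arms. If the all-available-data sentences govern, no patient is lost. The 20% is inferred from 12 and 15, and the simulated mechanisms are assumptions rather than trial figures. The protection that cLDA offers also holds only under missing at random.

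**What to change.** Delete the qualifier that limits the analysis to patients whose outcomes are complete, and replace the population and missing-data sentences with one rule. For example: *The primary analysis is a likelihood-based cLDA of all available FMA-UE data from every randomised patient, in the arm assigned, without prior imputation. Imputation is used only in a sensitivity analysis, to be specified before any outcome data are examined by arm.*

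The missed-visit sentence can stay, because it already agrees with this. Covariance structure, degrees of freedom and the form of the sensitivity analysis can be left to the statistical analysis plan. The cost is a change of wording and one sensitivity analysis, with no effect on recruitment, visits or data collection.
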